### Statistical Analysis

Differences in vABI and IHTT will be analyzed between the pre-treatment (T0), post-treatment (T1), and follow-up (T2) phases for both groups of patients (group r -TMS + TCC and SHAM + TCC group) to evaluate neurophysiological correlates of LHSN in the two groups.

In randomized controlled trials, the recommended statistical procedure to test pre-, post-treatment, follow-up control group design is the analysis of covariance (ANCOVA) (36, 37). In the context of ANCOVA, post-treatment and follow-up are considered dependent variables with pre-treatment variables as covariate (36, 37). However, ANCOVA requires the satisfaction of two assumptions, i.e., homogeneity vs. heterogeneity of the population at the pre-treatment time point and normal data distribution. In the present study, we will verify first the two ANCOVA assumptions for each outcome measure and, afterward, we will adopt the appropriate corrections and statistical approaches as follows:

Homogeneity vs. heterogeneity test: For each outcome, homogeneity of regression slopes will be verified (38): i.e., the values of *b* should not be significantly different between groups. If the assumption is violated, a CHANGE measure (i.e., a score of gain in the specific outcome) will be considered in a two × two mixed-model ANOVA with the between factor group and the within factor time (post-treatment and follow-up).Normal distribution test: Normal distribution will be verified (i.e., Kolmogorov-Smirnov test larger than 0.05) (36, 37) for each outcome variable. In case the assumption is violated, a linear logistic transformation will be performed.

If ANCOVA assumptions are verified for the primary outcome, we will analyze covariance for each neurophysiological index using a mixed-model ANCOVA with a 2X3 design. The “between” factor will be represented by the randomization group (rTMS, SHAM), whereas the “within” factor will be the assessment time (T1, T2) with T0 as a covariate. Whenever necessary, Greenhouse-Geiser correction will be applied, and corrected *p*-values will be reported in the ANCOVA. Further adjustments will be made for other possible confounding factors such as age, gender, education of the participants, and lesion location (if heterogeneity between participants in lesion locations emerges from clinical data). Besides *p*-values, effect sizes will be provided to assess the size of the treatment effect. Similar analyses will also be performed for clinical and motor outcomes after verification of ANCOVA assumptions. The BIT, the TEA, the CBS, and the motor function tests provide standard scores, separated for each test, and scores including a general performance with cut-offs that allow discriminating pathological performance. Several mixed-model ANCOVAs will be applied for every test in the 2X3 design described above. Finally, we will perform correlation analyses (both parametric and non-parametric) to evaluate the relations between the neurophysiological indices and clinical measures.

Two-tailed *t*-tests for independent samples will be employed to investigate the differences between groups. Data analysis will be performed using MatLab (The Mathworks Inc.) and SPSS (version 13). A significance level of 5% (i.e., *p*-value = 0.05), corrected for multiple comparisons when needed, will be accepted.

Additional clinical and demographic information, such as handedness of subjects, prescribed medications, and relevant medical conditions, will be recorded for each participant in specific Case Report Forms.

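### The normality check is applied to each raw outcome, not to the ANCOVA residuals, so it can miss non-normal errors and can fire on a skewed baseline

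*Protocol article*

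**What the plan says.** All of this stands in the Statistical Analysis section of the protocol article.

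- **The assumption.** The article says that "ANCOVA requires the satisfaction of two assumptions, i.e., homogeneity vs. heterogeneity of the population at the pre-treatment time point and normal data distribution". Normality is required of the data; errors and residuals are not mentioned.
- **The order.** The check comes before the analysis is chosen: "we will verify first the two ANCOVA assumptions for each outcome measure and, afterward, we will adopt the appropriate corrections".
- **The test, its target and its consequence.** "Normal distribution will be verified (i.e., Kolmogorov-Smirnov test larger than 0.05", and this is done "for each outcome variable. In case the assumption is violated, a linear logistic transformation will be performed".
- **The model it guards.** In the ANCOVA, "post-treatment and follow-up are considered dependent variables with pre-treatment variables as covariate". For the primary indices the between factor is the randomised group, and "the “within” factor will be the assessment time (T1, T2) with T0 as a covariate". This model is used only on a condition: "If ANCOVA assumptions are verified for the primary outcome, we will analyze covariance for each neurophysiological index using a mixed-model ANCOVA". Similar analyses follow for the clinical and motor scores.

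Nothing in the article redirects the normality check to residuals.

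**The concern.** The rule asks one question and tests another. The normal-theory tests in ANCOVA rest on the distribution of the errors once group and T0 have been accounted for. The raw outcome is the sum of a part predicted by T0, a group shift and the error, so its shape can differ from that of the error in either direction:

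- If T0 is close to normal and strongly predictive, it dilutes a non-normal error, and the outcome looks acceptable.
- If T0 is skewed and strongly predictive, the outcome is skewed even when the errors are perfectly normal.
- If the test pools the arms, the treatment effect is part of what is tested, so the result depends on the effect under study.

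At stake is the reliability of a switching rule that covers vABI, IHTT and every clinical and motor score. It can rescale an outcome, and so change what the treatment contrast means, when the planned model was sound. It can also lead the report to call the assumption verified after a test with little chance of seeing it fail.

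**Working it through.** **Sample size at which the rule operates (Sample Size section).** The article states a multiplier of 10.5, the values 2.1 and 2.8, and a result of 24. With 2.1 as a standard deviation and 2.8 as a difference:

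- n per arm = 2 × 10.5 × 2.1² / 2.8² = 92.61 / 7.84 = 11.8, so 12 per arm and 24 in total.
- With 10% loss: 12 / 0.9 = 13.3, so 14 per arm and 28 enrolled.

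This reproduces the article's figures and implies a design effect of 2.8 / 2.1 = 1.33 SD. The article labels the two values as squared quantities. Read that way, the effect would be √(2.8 / 2.1) = 1.15 SD. That labelling is a separate matter; results are given below for no effect and for 1.33 SD.

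**Model for the check (assumed).** Y = β·T0 + √(1 − β²)·e + d·group, with T0 and e independent and of unit variance, so that the within-arm SD of Y is 1. The article gives neither β nor any distribution shape. One post-treatment time is used, and the outcome test pools both arms.

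**Why the two targets differ.** Third moments of independent parts add, so within an arm

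skewness(Y) = β³·skewness(T0) + (1 − β²)^1.5·skewness(e).

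An exponential variable has skewness 2. At β = 0.8:

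- Exponential errors, normal T0: 0.36^1.5 × 2 = 0.216 × 2 = 0.43. Only about a fifth of the error skewness reaches the outcome.
- Exponential T0, normal errors: 0.512 × 2 = 1.02 in the outcome, although the model is correct.
- The second figure falls to 0.125 × 2 = 0.25 at β = 0.5.

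**Simulation.** 12 per arm, 20,000 replicates per row, Kolmogorov-Smirnov test at 0.05 with the Lilliefors correction. Entries are the percentage of trials in which normality is rejected.

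| T0 | Errors | β | d (SD) | Raw outcome | Residuals of Y on group and T0 |
|---|---|---|---|---|---|
| normal | exponential | 0.8 | 0 | 8 | 52 |
| normal | exponential | 0.8 | 1.33 | 5 | 51 |
| normal | exponential | 0.5 | 0 | 28 | 52 |
| normal | exponential | 0.5 | 1.33 | 10 | 52 |
| normal | exponential | 0.3 | 0 | 50 | 52 |
| normal | exponential | 0.3 | 1.33 | 13 | 51 |
| exponential | normal | 0.8 | 0 | 20 | 5 |
| exponential | normal | 0.8 | 1.33 | 8 | 5 |
| exponential | normal | 0.5 | 0 | 6 | 5 |
| exponential | normal | 0.5 | 1.33 | 5 | 5 |
| normal | normal | 0.8 | 0 | 5 | 5 |

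Smaller separate runs agree: 5% to 9% against 46% to 52% for exponential errors at β = 0.8, and 7% to 20% against 5% for exponential T0 at β = 0.8. With N = 28, exponential errors and β of 0.7 to 0.9, the detection rates are 6% to 13% on the outcome and 60% on residuals.

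**The uncorrected test.** If the mean and SD are estimated from the data and the standard Kolmogorov-Smirnov table is used, the critical distance at n = 24 is 0.269 instead of 0.176. Under normality the test then rejects in about 0% of trials. Even on residuals it detects exponential errors in only about 3% to 5% (N = 24 and 28). The article does not say which version is meant.

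**Effect on the treatment test.** Type I error stays near 5% under either target. For exponential errors and a 0.6-SD effect, with a logit-type transformation as fallback, power is 68% with the outcome as trigger and 64% with residuals, so residuals bring no consistent gain.

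**The case against.** The strongest reply is that this is a weaker diagnostic without a demonstrated inferential cost, and much of that stands.

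- **Power.** A reader might infer that testing the wrong quantity loses power. The documents do not support this. The stated fallback is a transformation, and with a logit-type one no consistent loss appears. A gap arises only if one substitutes a procedure that the article does not name: a Mann-Whitney test on residuals gives 69% against 76% for a 0.6-SD effect. With Quade's rank ANCOVA the figures are 69% and 67%. At the design effect of 1.33 SD and slope 0.8, power is 99% under both triggers with each of these rank-based fallbacks.
- **Type I error.** A reader might also infer inflation. None is seen.
- **Dependence on inputs.** The contrast is large only when T0 predicts the outcome well or the treatment effect is large. At slope 0.3 with no effect, the two targets perform almost alike. So the check *can* miss non-normal errors; it does not always do so. At the design effect, however, it detects them in only 13% even at slope 0.3.
- **Simplifications.** The simulation has one post-treatment time, whereas the plan has two. It also pools the arms, which the article does not specify. Testing each arm separately would remove the group shift but leave the T0 part in the outcome.
- **Target versus test.** If the uncorrected Kolmogorov-Smirnov test is used, moving to residuals alone repairs little. This is correct and shapes the fix.

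A condensed article may leave details to a fuller document. Here, though, the assumption, test, threshold, target and consequence are all stated, and the target is the wrong one.

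**Conclusion.** The point holds, as a minor one. The stated rule tests a quantity that ANCOVA does not require to be normal. At 12 per arm with Lilliefors p-values:

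- It detects exponential errors in about 5% to 8% of trials at slope 0.8, against about 50% on residuals. At the 1.33-SD design effect it detects them in 5% to 13% across slopes 0.3 to 0.8.
- With a skewed T0 and sound errors it fires in about 7% to 20% at slope 0.8, against 5%. At slopes of 0.5 or below this false firing essentially vanishes.

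These sizes rest on assumed slopes and error shapes and on reading 2.1 and 2.8 as an SD and a difference. The direction of the problem does not. The harm is limited to a switching rule that can rescale a sound analysis, or declare an assumption met when it fails. It would be wrong to conclude that the primary comparison is biased, underpowered or anti-conservative for this reason.

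**What to change.** Two wording changes in the Statistical Analysis section:

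1. State the assumption as normally distributed residuals instead of normality of the data.
2. Replace the check on each outcome variable by one on the residuals of the fitted model with group, time and T0. Use a normal plot together with Shapiro-Wilk or a Lilliefors-corrected Kolmogorov-Smirnov test, and base any change of analysis on that check.

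The test has to change along with its target, because the uncorrected Kolmogorov-Smirnov test almost never rejects at 24 to 28 patients.

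The cost is editorial. The residuals come from a model that is already planned, and no patients, visits or measurements are added.

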**Figure 2 F2:**
[figure not shown]
Visual detection task. A fixation cross is presented on a black background during the whole task. At the beginning of a trial, a stimulus is presented randomly for 96 milliseconds (ms) either on the fixation point's left or right. Before a new trial begins the fixation cross is again presented for 1,000 ms.

The EEG will be recorded from 18 Ag/AgCl-cup electrodes according to the 10/20 system referenced to the linked ear lobes. The EEG signal will be recorded from electrodes: Fz, Cz, Pz, C4, C3, P4, P3, F4, F3, Oz, O1, O2. The negative peak of the N1 will be considered to analyze amplitude in microvolt (μv) and latency in milliseconds (ms). N1 amplitude and latency will be analyzed separately for left and right-presented stimuli over P3 and P4 (13, 17). Then, indexes of inter-hemispheric imbalance will be extracted. In particular, the Visuospatial Attention Bias Index (vABI; 13) and the Interhemispheric transmission time [IHTT, (27)], which are based, respectively, on N1 amplitude and latency.

The vABI will be extracted in two steps. First, we will calculate the averaged activities of the N1 for stimuli presented on both sides from considered electrodes (i.e., mean of P3 and P4). These averaged activities will measure the two hemispheric activations after lateralized stimulus presentation. The individual differences in the activations for lateralized stimuli will be calculated according to the following formula: vABI = N1 amplitude for right stimuli - N1 amplitude for left stimuli. The vABI will be calculated as a lateralization index (32) on N1 amplitude. Such an index can measure imbalance for left and right stimuli processing as it measures the activation of the two hemispheres in response to lateralized stimuli.

Similarly, based on N1 peak latency, we will compute the IHTT (27, 28), an indicator of the EEG signal's transmission times from one hemisphere to the other. In particular, IHTT measures the difference between N1 latencies for left presented stimuli on the posterior electrodes P3 and P4 (i.e., left IHTT = N1 latency on P4 - N1 latency on P3), thus constituting a single index in milliseconds of the inter-hemispheric transmission times specifically for left presented stimuli (13).

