## Data Analysis

### Sample Size

The sample size was calculated using the following formula:

$$\begin{array}{l} n=\frac{2{\left(z_{\left(1-\alpha \right)}\;+z_{\left(1-\beta \right)}\right)}^{2\;}\sigma^{2}}{\delta^{2}} \end{array}$$

Where *N* is the sample size; σ2: population variance established by previous studies = 2.1; δ2: absolute error allowed for parameter estimation for vABI = 2.8; z: constant (corresponding to the value of the standardized normal random variable) that depends on the level of confidence desired for the estimation. Fixing α = 0.05 and 1 – β = 0.80, (Z_1−α_ + Z_1−β_) ^2^ = 10.5. The sample size resulting from the formula is 24. Consequently, the minimum sufficient sample to reach all aims is, assuming 10% of subjects lost to follow-up, 28 subjects (14 X group), enrolled over 1 years. In case of recruitment delays, a multicentric extension of the study will be considered to guarantee an adequate number of participants.

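### The fallback for non-normal data, a linear logistic transformation, does not fit the primary outcomes, which are signed differences in microvolts and milliseconds

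*Protocol article*

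**What the plan says.** In the Protocol article, Statistical Analysis, two assumptions are to be checked for each outcome before the ANCOVA is run. The second is normality: "Normal distribution will be verified (i.e., Kolmogorov-Smirnov test larger than 0.05". The remedy is one sentence: "In case the assumption is violated, a linear logistic transformation will be performed". No formula, bounds, offset or rescaling is given, and no other remedy for non-normality follows. The mixed-model ANCOVA with T0 as covariate is then described for the case in which the assumptions are met.

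The Primary Endpoint section, in the text after Figure 2, defines the two indices:

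- Amplitude: "vABI = N1 amplitude for right stimuli - N1 amplitude for left stimuli"
- Latency: "left IHTT = N1 latency on P4 - N1 latency on P3"

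The units are fixed in the same place: "The negative peak of the N1 will be considered to analyze amplitude in microvolt (μv) and latency in milliseconds (ms". The text calls vABI a lateralization index, but the printed formula is a plain difference and not a ratio. Both indices can be negative, zero or larger than 1.

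**The concern.** A logistic transformation in the usual statistical sense is a logit, ln(x/(1-x)), which is meant for proportions. Neither primary outcome is a proportion. If the normality check fails for vABI or IHTT, the article names a method that does not suit the variable, and someone must decide what the phrase means. In a trial of 28 patients, that choice can affect the result. Unless it is fixed elsewhere beforehand, it could be made with the data in view. The treatment effect would also no longer be in microvolts, the unit of the difference of 2.8 used for the sample size.

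The trigger is a second weakness. ANCOVA assumes approximately normal residuals given group and T0, whereas the article tests each outcome variable. It also does not say which form of the Kolmogorov-Smirnov test applies when the mean and SD are estimated from the same data.

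**Working it through.** **Inputs.** From Sample Size: "population variance established by previous studies = 2.1", "absolute error allowed for parameter estimation for vABI = 2.8", the constant 10.5 and a total of 24 (28 after losses, 14 per group). The documents give no mean for vABI and no mean or SD for IHTT, so those below are assumptions.

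**Is 2.1 an SD or a variance?** The plan's own figure does not settle it.

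- Read as SD and difference, with 10.5: 2 × 10.5 × 2.1² / 2.8² = 11.81, so 12 per group and 24 in total.
- Read as labelled (both already squared), with 10.5: 2 × 10.5 × 2.1 / 2.8 = 15.75, so 16 per group and 32 in total.
- Read as labelled, with 7.85 (the two-sided 5%, 80% power constant): 2 × 7.85 × 2.1 / 2.8 = 11.78, so 24 in total again.

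Both readings are therefore carried: SD = 2.1, and SD = √2.1 = 1.45.

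**Reading 1: logit.** It is defined only for 0 < x < 1. For a normal vABI with mean m and SD s, the share with a logit is Φ((1-m)/s) - Φ((0-m)/s).

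| Mean (assumed) | SD 2.1: has a logit | no logit | SD 1.45: has a logit | no logit |
|---|---|---|---|---|
| 0 | 0.683 - 0.500 = 18.3% | 81.7% | 0.755 - 0.500 = 25.5% | 74.5% |
| 1.4 | 0.4245 - 0.2525 = 17.2% | 82.8% | 0.391 - 0.167 = 22.4% | 77.6% |
| 2.8 | 0.1957 - 0.0912 = 10.4% | 89.6% | 0.107 - 0.027 = 8.0% | 92.0% |

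The most favourable mean for a logit is 0.5. Even there the shares with a logit are only 18.8% and 27.0%. At a mean of -2.8 they are 5.6% and 2.2%. For IHTT, with assumed means of 5 to 20 ms and SDs of 10 to 15 ms, 0.6% to 3.6% of values lie between 0 and 1.

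**Reading 2: logarithm (a possible slip of wording).** It is undefined at or below zero. With SD 2.1, 50%, 25% and 9% of vABI values are at or below zero at means 0, 1.4 and 2.8. The chance that at least one of 28 values fails is 1 - (1-p)²⁸, which at mean 2.8 is 1 - 0.909²⁸ = 93%, and it is higher at the other two means. With SD 1.45 and mean 2.8 the chance is 53%. At an assumed mean of 5.6 it falls to 10% (SD 2.1) or 0.2% (SD 1.45), so this reading fails often but not always.

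**Reading 3: logistic function, 1/(1+exp(-x)).** It is finite for every real value. It squeezes the data into 0 to 1 and does not normalise them. In simulated right-skewed samples of 28, Shapiro-Wilk rejected normality in 95% before the transformation and 94% after. For IHTT in ms (assumed mean 10 with SD 10, or mean 20 with SD 15), 78% to 90% of transformed values lie below 0.01 or above 0.99.

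**Reading 4: logit after linear rescaling to the sample range.** The sample minimum becomes 0 and the maximum 1, so 2 of 28 values are infinite. Fixed outer bounds would cure that, but none are stated.

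**The trigger.** Simulated exponential data were tested at 5% with the mean and SD estimated from the sample:

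| n | Uncorrected test rejects | Lilliefors-corrected test rejects |
|---|---|---|
| 14 | about 1% | about 41% |
| 28 | about 10% | about 74% |

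For the same clearly skewed data, whether the fallback fires depends mainly on a choice that the article does not state.

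**The case against.** Five points can be made for the plan.

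1. **The transformation can be computed on some readings.** This stands. A logistic function exists for any real number, and so does a logit after rescaling to fixed bounds. A reader might infer that the transformation is impossible, but the wording does not force the plain logit. The defect is that the rule is undefined as written and unsuitable on its plain readings.

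2. **It is only a conditional branch.** This also stands. The main analysis is ANCOVA on the untransformed indices. A reader might infer that the primary analysis would stop. The documents do not support that, because the branch applies only if the test rejects, and the uncorrected test seldom does at this sample size.

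3. **A real treatment effect would not set off the fallback.** A reader might infer that a working treatment makes the pooled outcome non-normal and so triggers the rule. The article does not say that the groups are pooled. Even if they are, with two equal normal groups separated by the planned difference (24 or 28 in total, 2.1 and 2.8 read either way), the Lilliefors-corrected test rejected in 3.8-5.0% of simulated samples. With no effect it rejected in 4.6-5.0%. The uncorrected test rejected in under 0.1%. The argument fails.

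4. **The percentages rest on assumptions.** True, and they are labelled so above. The 2.8 is a planned difference and not a mean, and the article calls 2.1 a variance. The direction is the same under every combination tried.

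5. **Details belong in the analysis plan.** Bounds or an offset might be set in a plan that is not shown, so it cannot be said that the scale would be chosen after seeing the data. But the article does not leave the method open. It names one, for every outcome variable, and that method does not suit the endpoints that the same article defines.

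**Conclusion.** The point holds in limited form. The stated remedy for non-normality does not fit vABI or left IHTT. As a logit it is undefined for about 82-90% of vABI values if 2.1 is an SD, and about 75-92% if it is a variance, for normal data with assumed means of 0, 1.4 and 2.8. For IHTT the figure is above 96% under the assumed means and SDs. As a log it fails wherever a value is at or below zero. As a logistic function it is computable, but it is not a normalising transformation and it gives up the microvolt or millisecond scale. The trigger looks at the raw outcome and not the residuals, and its behaviour depends on the unstated version of the test.

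The weakness is confined to a fallback branch. The planned T0-adjusted analysis on the raw scale is not itself in question here.

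**What to change.** Delete the Kolmogorov-Smirnov gate and the transformation sentence. State instead that:

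- vABI and IHTT are always analysed on the raw scale with T0 as covariate, so that effects are reported in microvolts and milliseconds.
- Residuals from that model are inspected graphically, and the result does not switch the primary analysis.
- The pre-specified robustness analysis is a permutation p-value for the T0-adjusted group effect, re-randomising within the randomisation blocks.

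If the 2:2 list means blocks of four, each block has 6 possible allocations. Seven blocks (28 patients) then give 6⁷ = 279,936, which is ample for a permutation test. Another method valid for signed data, such as a rank-based or robust ANCOVA, would also serve if it is named in advance.

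The cost is a few sentences in the protocol or analysis plan and a few lines of code. Patients, visits, measurements and sample size are unaffected.

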According to this preliminary evidence, this study's central hypothesis is that LHSN symptoms in both stroke and TBI rely on similar neurophysiological correlates. Indeed, as observed for right hemisphere strokes, LHSN in TBI patients may be caused by an imbalance in inter-hemispheric activity due to the left hemisphere's hyperactivity (12, 21). Consequently, i-rTMS might have a rebalancing effect by inhibiting this hyperactivity, reducing LHSN symptoms and related disability in TBI patients.

Thus, the general aim of this randomized controlled trial is to test the efficacy of a novel therapeutic approach based on i-rTMS applied to the left PPC followed by a visual scanning treatment (VST) in comparison to the same cognitive treatment preceded by a sham stimulation on neurophysiological and clinical correlates of LHSN in a sample of TBI patients. In particular, this study's specific aims are (1) to assess the efficacy of i-rTMS applied to the left PPC + VST on the inter-hemispheric imbalance in patients affected by LHSN after TBI. In doing so, we will make use of measures of interhemispheric functional connectivity derived from N1. (2) To detail the effect of combined i-rTMS + VST on cognitive symptoms of LHSN in TBI patients as measured by specific clinical measures. (3) To assess whether the effect of the combined i-rTMS + VST treatment has the potential to promote long-lasting lessening of the behavioral manifestations of LHSN in activities of daily living.

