## Discussion

Many published studies have highlighted the efficacy of different rehabilitation methods for LHSN syndrome after stroke (10). However, scientific evidence is still low in TBI patients, given factors such as low sample size, methodological bias (lack of double-blind studies or follow-up assessments), and contradictory results.

This study's rationale is that neuronal loss due to TBI leads to an impairment of cognitive functions due to a deficit in the related neuro-functional networks. Thus, the reactivation of those networks may allow the empowerment of the compromised functions. Unlike the traditional rehabilitation methods, the new magnetic stimulation techniques, such as i-rTMS, allow the execution of a cognitive task through the pre-empowerment of a specific network or neuronal circuit. This priming may facilitate experiential learning with a richer and more articulated neural environment and selectively stimulate according to the areas most involved in the lesion. In TBI, the mechanism of empowerment concerns the preserved areas and the inter-neuron connectivity between those areas. Consequently, i-rTMS could increase the “responsiveness” of the peri-lesional areas and the inter-hemispheric connectivity during cognitive training, increasing its effectiveness compared to the SHAM condition.

Therefore, the current project's main expected outcome will provide evidence, on a large sample of TBI patients, of the inter-hemispheric functionality underlying cognitive symptoms of LHSN. It will also point out the specific effect of i-rTMS protocols on the inter-hemispheric imbalance. In particular, we expect to observe in the treatment group a larger rebalancing effect than in the control group, as demonstrated by smaller amplitudes of vABI and earlier latencies of IHTTs at the post-treatment assessment. Furthermore, we expect to observe the persistence of this effect at follow-up. Additionally, we expect to observe larger improvements in cognitive and behavioral symptoms of LHSN induced by the i-rTMS compared to the control group, as demonstrated by better performances on clinical tests and batteries (10).

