To our knowledge, this study will be the first to provide an evidence-based theory on the inter-hemispheric functionality in TBI patients with LHSN, providing clinicians with a new framework for approaching, studying, and interpreting LHSN with innovative markers on neurophysiological activity. Moreover, the evaluation of rehabilitation effects of i-rTMS on the visuospatial inter-hemispheric network and cognitive and activities of daily living measures of LHSN will provide the basis to understand how i-rTMS influences LHSN in TBI patients. This novel knowledge, in turn, will create the basis for the development of new treatment strategies, which will have the potential to lessen the impact of LHSN-related disability for TBI patients and their families.

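### Index–symptom correlations without a term for randomised group would partly restate the treatment effects if post-treatment values from both arms are pooled

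*Protocol article*

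**What the plan says.** After describing the ANCOVAs, the Statistical Analysis section of the protocol article adds that "we will perform correlation analyses (both parametric and non-parametric) to evaluate the relations between the neurophysiological indices and clinical measures". It does not say which time points are used, whether values or changes are correlated, whether the arms are taken together, or whether anything is adjusted for. For the ANCOVAs, the same section specifies randomisation group as a factor, T0 as a covariate, and further adjustment for age, gender, education and possibly lesion location.

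The Discussion states what the trial expects of each set of measures. For the neurophysiological indices, "we expect to observe in the treatment group a larger rebalancing effect than in the control group". For the clinical measures, "we expect to observe larger improvements in cognitive and behavioral symptoms of LHSN induced by the i-rTMS compared to the control group".

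The Blinding section places the T0 assessment before randomisation.

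**The concern.** After treatment, the sample is a mixture of two arms. If active stimulation moves the index and also moves the clinical score, patients in one arm tend to differ from those in the other on both measures. That difference alone correlates them, whatever the relation among patients treated alike. A test of zero correlation in the mixed sample is then a test of a null hypothesis that the trial's own expectations make false.

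The primary endpoint is neurophysiological and the clinical measures are secondary. Each ANCOVA handles one outcome at a time, so these correlations are the only analysis in the article that sets index against symptom. A significant result would be read as a sign that the index tracks symptoms, when it could be largely the two treatment effects seen again.

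**Working it through.** **Inputs from the Sample Size section.** "population variance established by previous studies = 2.1"; "absolute error allowed for parameter estimation for vABI = 2.8", labelled there as δ²; "Fixing α = 0.05 and 1 – β = 0.80"; a printed multiplier of 10.5; 24 patients before dropout and 28 (14 per arm) after 10% loss.

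**The plan's own figure.** n per arm = 2 × multiplier × σ²/δ².

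- Variance 2.1, δ² = 2.8, two-sided 5% and 80% power (multiplier 7.85): 2 × 7.85 × 2.1/2.8 = 11.8, so 12 per arm and 24 in total. The standardised effect is √(2.8/2.1) = 1.155.
- SD 2.1, difference 2.8, printed multiplier 10.5: 2 × 10.5 × 4.41/7.84 = 11.8, again 24 in total. The standardised effect is 2.8/2.1 = 1.333.
- Dropout: 24/0.9 = 26.7, so 27, or 28 for equal arms.

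Two readings therefore return 24, and they give index effects of 1.155 and 1.333 SD. (The printed 10.5 with σ² = 2.1 and δ² = 2.8 gives 15.75, so 16 per arm and 32 in total. That is a separate matter and does not affect this point.)

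**Pooled correlation with no association within arms.** For equal arms, unit SD within arm, and shifts d₁ (index) and d₂ (score):

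|r| = (d₁d₂/4) / √[(1 + d₁²/4)(1 + d₂²/4)]

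- 1.155 on both: 0.333/1.333 = 0.25
- 1.333 on both: 0.444/1.444 = 0.31
- 1.333 and 0.8: 0.267/√(1.444 × 1.16) = 0.21
- 1.333 and 0.5: 0.167/√(1.444 × 1.0625) = 0.13
- 0.5 on both: 0.0625/1.0625 = 0.06
- 1.333 and 0: 0

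**Rejection rates.** Simulation with normal data, zero within-arm correlation and two-sided 5% tests (200,000 trials per setting). The clinical shifts are assumptions, because the article gives none.

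| Index shift (SD) | Score shift (SD) | Pooled Pearson, 12 per arm | Pooled Pearson, 14 per arm | Partial on group |
|---|---|---|---|---|
| 1.333 | 1.333 | 33% | 38% | 5% |
| 1.155 | 1.155 | 23% | 26% | 5% |
| 1.333 | 0.8 | 17% | 19% | 5% |
| 1.333 | 0.5 | 10% | 11% | 5% |
| 0.5 | 0.5 | 6% | 6% | 5% |
| 1.333 | 0 | 5% | 5% | 5% |

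Spearman does not help: with 14 per arm it rejects in about 27% and 40% at 1.155 and 1.333 SD on both measures. The partial Spearman correlation adjusted for group stays at 5%. Adding the T0 values of both measures, with an assumed T0-to-T1 correlation of 0.5, leaves the rate at about 5% to 6%.

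**The case against.** The strongest reply is that the article does not say the arms are pooled. Partial, per-arm, T0-only and change-score correlations all fit its sentence, and the full protocol or analysis plan, neither of which is shown, may settle the matter. This stands as a limit on confidence. It does not remove the point: correlation is the method named, the ANCOVAs beside it are given a group factor and covariates while the correlations are given none, and nothing restricts them to T0.

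A reader might infer that any effective treatment makes the pooled test misleading. It does not. The treatment must shift both measures: with an effect on the index alone the rate stays at 5%, and modest effects on both do little.

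A reader might also infer that the trial's claims about mechanism rest on these correlations. The article does not support this. The hypothesis that "i-rTMS might have a rebalancing effect by inhibiting this hyperactivity, reducing LHSN symptoms and related disability in TBI patients" is about a treatment effect. The statement that the work "will provide the basis to understand how i-rTMS influences LHSN in TBI patients" has as its subject the evaluation of treatment effects on the network and on the clinical measures. None of the three specific aims is an index–symptom correlation.

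A much larger bias can be obtained by taking a difference of 2.8 with a variance of 2.1, which is an effect of 2.8/√2.1 = 1.93 SD. That reading gives 2 × 10.5 × 2.1/7.84 = 5.6, so 6 per arm and 12 in total. It contradicts the stated 24 and is not used here.

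Finally, all rates above are at an uncorrected 5%. The article provides for multiplicity correction where needed, which would lower them but would not remove the correlation that pooling creates.

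**Conclusion.** The point holds as a matter of method for a secondary, supporting analysis. Correlations of post-treatment or change values over both arms, without a group term, can be significant with no association among patients within either arm. At the index effects implied by the article's own sample size, and with an equally large clinical effect, this happens in about 23% to 38% of trials with 12 to 14 per arm. With a clinical effect of 0.8 SD and an index effect of 1.333 SD it is about 17% to 19%, and at 0.5 SD on both it is close to nominal.

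This rests on three assumptions: the arms are taken together, values after T0 are used, and the clinical effect is as stated in each line. T0 correlations cannot carry a treatment effect and are sound as they are. The primary comparison, the endpoints and the sample size are untouched.

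**What to change.** State the time points for the correlations. For T1 and T2 values, or changes, use partial Pearson and partial Spearman correlations of index and clinical score adjusted for randomised group. Keep unadjusted correlations for T0 only. Add that correlations pooled over arms after treatment will not be presented as evidence that the index tracks symptoms.

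Further adjustment for the T0 values of both measures is optional. It asks a different question, namely association beyond baseline, and takes out any stable association already present at T0, so the choice should be deliberate.

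The cost is a sentence or two in the analysis section, data that are already collected, and one degree of freedom (21 instead of 22 with 12 per arm). Reported correlations may be lower than pooled ones when the treatment works.
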